**Methods:**

This is a single-center, single-blind, randomized controlled trial. Seventy tracheostomized patients (aged 40–70 years, with tracheostomy for 1–3 months) will be randomly assigned to either the HI-IMT group or the control group. The HI-IMT group will receive IMT at 50% of the maximal inspiratory pressure (MIP), 30 breaths/day, 5 days/week for 2 weeks. The control group will receive sham training, which will involve performing the same breathing cycles without any applied resistance. Both groups will receive standard care, including pharmacological therapy, rehabilitative nursing, and basic rehabilitation exercises. Diaphragmatic function, airway clearance ability, anxiety levels, and quality of life will be assessed using the MIP% predicted (primary outcome) and peak inspiratory flow (PIF), the Semi-Quantitative Cough Strength Score (SCSS), the standardized Zung Self-Rating Anxiety Scale (SAS), and the Tracheostomy-Specific Quality of Life (TQOL) scale. Additionally, decannulation rates and adverse events will be systematically recorded throughout the study period. Data will be analyzed using parametric or non-parametric tests for unadjusted between-group comparisons. All analyses will adhere to the intention-to-treat principle, with a *p*-value < 0.05 set for statistical significance.

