#### Primary outcome

The primary outcome of this study is the change in the MIP % predicted from baseline to the post-intervention timepoint (Week 2). MIP is a widely recognized and reliable indicator for assessing diaphragmatic function [37, 38]. Raw MIP scores were standardized according to the method of Evans and Whitelaw (males = 120 **−** (0.41** × **age); females = 108 **−** (0.61** × **age)) [39]. To account for established variations in MIP attributable to age and gender, the results are expressed as a percentage of predicted values.

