### Sample size calculation {14}

The sample size was determined based on the primary outcome (change in MIP% predicted). Using data from Bissett et al.’s RCT where high-intensity IMT demonstrated a mean improvement of 17% (SD = 4%) versus 6% (SD = 3%) in controls [24], we conservatively estimated a mean difference of 8% between groups. To account for greater clinical heterogeneity in tracheostomized patients, we adopted a pooled SD of 9% (versus 3.54% in Bissett’s study). Using G*Power 3.1 with a two-tailed *t*-test (*α* = 0.05, power = 0.90, allocation ratio 1:1), the initial calculation indicated 28 participants per group (total *N* = 56). Considering a 20% attrition rate (based on Bissett’s reported 17% loss to follow-up), the adjusted sample size was 35 per group (total *N* = 70).

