## Statistical methods

### Statistical methods for primary and secondary outcomes {20a}

Statistical analyses will be conducted in accordance with the CONSORT guidelines to ensure methodological transparency and rigor [45]. The primary analytical approach will follow the intention-to-treat (ITT) principle, including all randomized participants irrespective of adherence to the intervention. In cases where the percentage of missing data exceeds 20%, multiple imputation will be applied using predictive mean matching for continuous variables. Sensitivity analyses will also be conducted, comparing ITT and per-protocol (PP) populations. The PP population will consist of participants who complete at least 80% of the scheduled training sessions, enabling evaluation of result robustness.

The data will be analyzed with SPSS version 26.0. The normality of continuous variables will be assessed using the Shapiro–Wilk test and visual inspection of histograms. Between-group differences in the MIP will be analyzed with independent samples *t* tests (for normally distributed data) or Mann–Whitney *U* tests (for nonnormally distributed data). The secondary outcomes will be analyzed as follows: continuous variables will be compared between groups with t tests or Mann–Whitney *U* tests on the basis of distributional assumptions. Ordinal outcomes will be evaluated with Wilcoxon rank-sum tests. Binary outcomes will be analyzed with chi-square tests or Fisher’s exact tests for small sample sizes. Adverse events will be summarized descriptively by frequency and severity.

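### The primary test names MIP where the primary outcome is change in MIP% predicted, and it is fixed as unadjusted although every participant has a baseline value: a consistency and efficiency point, not an invalid analysis

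*Protocol article*

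**What the plan says.** The protocol article describes the primary comparison in four places.

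- **Primary outcome:** "The primary outcome of this study is the change in the MIP % predicted from baseline to the post-intervention timepoint (Week 2"). The section adds that results are expressed as a percentage of predicted to allow for age and sex.
- **Sample size calculation {14}:** "The sample size was determined based on the primary outcome (change in MIP% predicted"). The inputs are "we conservatively estimated a mean difference of 8% between groups" and "we adopted a pooled SD of 9"%, with a two-tailed t test, α = 0.05 and power 0.90. This gives 28 per group, or 35 after 20% attrition.
- **Statistical methods {20a}:** "Between-group differences in the MIP will be analyzed with independent samples" t tests, or Mann–Whitney U tests if the data are not normal. The sentence mentions neither change nor percent predicted, and no covariate.
- **Abstract, Methods:** the primary outcome is given as "the MIP% predicted (primary outcome) and peak inspiratory flow (PIF"), without mention of change, and the analysis as "parametric or non-parametric tests for unadjusted between-group comparisons".

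Eligibility {10} requires MIP% predicted of at most 30%, so a baseline value exists for every participant. Sequence generation {16a} specifies simple 1:1 randomization of the 70 participants.

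**The concern.** There are two linked problems.

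**The analysed variable is not the defined one.** Section {20a} is where the primary test is specified, and taken alone its wording allows raw MIP in cmH₂O or MIP% predicted, and the Week 2 value or the change. Elsewhere the protocol uses MIP for the raw reading: the HI-IMT group description records the highest trial as the MIP and sets the training load from it. The candidate variables differ in scale and in SD. The SD of 9 was assumed for change in MIP% predicted, so the power statement belongs to that variable only.

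**The comparison is fixed as unadjusted.** The abstract states this outright; it is not a detail left to a later plan. Simple randomization of 70 people does not restrain chance baseline imbalance, and the analysis does not use the baseline beyond any subtraction in a change score. At stake are some precision and a clear statement of what will be estimated.

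**Working it through.** **1. The plan's own figure.** Inputs from {14}: difference 8, SD 9, two-sided α 0.05, 1:1 allocation, t test. With the noncentral t distribution, power is 0.893 at 27 per arm and 0.904 at 28. So n = 28, and 28 / (1 − 0.20) = 35. The stated sample size is correct for a t test on change. If all 35 per arm were analysed, power would be 0.956.

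**2. Raw MIP versus percent predicted.** The prediction equations in the Primary outcome section, at the age limits of 40 and 70, give:

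- males: 120 − 0.41 × 40 = 103.6 and 120 − 0.41 × 70 = 91.3 cmH₂O
- females: 108 − 0.61 × 40 = 83.6 and 108 − 0.61 × 70 = 65.3 cmH₂O

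The planned 8-point difference therefore equals 0.08 × 65.3 = 5.2 to 0.08 × 103.6 = 8.3 cmH₂O, depending on age and sex. The two scales are not interchangeable.

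**3. Assumptions for the rest.** The documents give no baseline SD (s₀) and no within-arm slope of Week 2 on baseline (b). The 30% entry cap limits s₀: a uniform spread over 0 to 30 has SD 30/√12 = 8.66, which is a generous value. I take s₀ = 4 to 8.66 and b = 0.6 to 1.0, and hold the change variance at 9² = 81.

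- Baseline-adjusted (ANCOVA) residual variance = 81 − (1 − b)² s₀²
- Week 2-only variance = 81 + (2b − 1) s₀²

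Power is for 28 per arm and a difference of 8, with 53 degrees of freedom for ANCOVA and 54 for the t test.

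| s₀ | b | ANCOVA variance | Ratio to 81 | ANCOVA power | Week 2-only variance | Week 2-only power |
|---|---|---|---|---|---|---|
| 4 | 0.6 | 78.44 | 0.968 | 0.913 | 84.2 | 0.893 |
| 4 | 1.0 | 81.00 | 1.000 | 0.904 | 97.0 | 0.847 |
| 6 | 0.6 | 75.24 | 0.929 | 0.923 | 88.2 | 0.879 |
| 6 | 1.0 | 81.00 | 1.000 | 0.904 | 117.0 | 0.776 |
| 8.66 | 0.6 | 69.00 | 0.852 | 0.943 | 96.0 | 0.851 |
| 8.66 | 1.0 | 81.00 | 1.000 | 0.904 | 156.0 | 0.653 |

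The t test on change has power 0.904 in every row. Baseline adjustment gains between nothing (slope 1) and about 15% of variance. A Week 2-only test has power of 0.65 to 0.89. Its variance exceeds 81 whenever b is above 0.5, so the shortfall depends on that assumption.

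**4. What adjustment settles.** With baseline in the model, the arm coefficient is the same whether the response is the Week 2 value or the change, because subtracting baseline alters only the baseline coefficient. That removes the Week 2-versus-change ambiguity. It does not decide between raw MIP and MIP% predicted; only naming the variable does.

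**The case against.** The case for leaving the plan alone is substantial. Under randomization, an unadjusted t test on change is unbiased. Chance baseline imbalance is already reflected in its standard error. The sample size calculation and the analysis use the same kind of test, and the target power is met without a covariate. A reader who takes {20a} together with the outcome and sample size sections would probably supply change in MIP% predicted. All of this stands, and it is why the point concerns consistency and efficiency. It does not justify leaving the sentence that specifies the primary test without the variable it tests.

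Three stronger readings are tempting, but the documents do not support them.

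- **Large precision gains.** The familiar ratio (1 + r)/2 for ANCOVA against change scores gives variance reductions of 35%, 25% and 15% at r = 0.3, 0.5 and 0.7. It assumes equal variances at both visits. With a change SD of 9, that implies a baseline SD of 9/√(2(1 − r)) = 7.6, 9.0 and 11.6. The last two exceed even the uniform value of 8.66 under the entry cap. The capped range above is the fairer guide, and its lower end is no gain at all.
- **Regression to the mean biases the result.** Selecting on a low baseline does produce regression to the mean, but in expectation equally in both arms, so the between-arm difference is not biased.
- **The trial is mis-sized or the test invalid.** Step 1 of the working shows otherwise.

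**Conclusion.** The point holds as a recommended change. Two facts are certain from the text: {20a} names MIP where the outcome and sample size sections specify change in MIP% predicted, and the abstract fixes an unadjusted comparison although the baseline is available for everyone. The t test on change would be valid, with power 0.904 at 28 per arm.

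The size of the benefit rests on assumptions. With a change SD of 9, a baseline SD of 4 to 8.66 and a slope of 0.6 to 1.0, adjustment saves 0 to 15% of variance and power is 0.904 to 0.943. The ambiguity could cost more than the missing covariate: if {20a} were carried out as a comparison of Week 2 values, power would be about 0.65 to 0.89 on the same assumptions, and the stated 90% would not apply.

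**What to change.** - In {20a}, replace MIP with MIP% predicted. Define the primary analysis as a linear model of Week 2 MIP% predicted (equivalently, its change from baseline) on arm and baseline MIP% predicted, reporting the adjusted mean difference with its 95% CI.
- In the abstract, delete the word unadjusted and describe the primary outcome as the change in MIP% predicted.
- Keep the unadjusted test on change as a supportive analysis. The sample size can stay as it is.
- Adjusting the continuous secondary outcomes for their own baselines in the same way is optional.

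**Cost.** One degree of freedom, and no new data. The edits are short but not free: recruitment began in August 2025, and section {25} requires ethics committee approval and a registry update for any protocol modification. The change should be made before any unblinded data are seen.

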#### Secondary outcomes

The secondary outcomes include changes in peak inspiratory flow (PIF), airway clearance ability, anxiety levels, quality of life, the decannulation rate, and the incidence of adverse events.

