##### Airway clearance ability

The Semi-Quantitative Cough Strength Score (SCSS) [41] is a 6-point ordinal scale (0–5) that has been validated for the assessment of cough efficacy as follows: 0: no cough; 1: visualized cough (oral airflow present) without sound; 2: barely audible cough; 3: distinctly audible cough; 4: forceful cough; and 5: sustained vigorous coughing. The SCSS will be assessed during brief manual occlusion of the tracheostomy stoma.

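### Cough strength (SCSS): the plan does not say whether the change or the Week 2 score is ranked, and the unadjusted rank-sum test uses the baseline score poorly on either reading

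*Protocol article*

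**What the plan says.** Four places in the protocol article bear on this point.

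- Secondary outcomes: "The secondary outcomes include changes in peak inspiratory flow (PIF), airway clearance ability, anxiety levels, quality of life", followed in the same list by the decannulation rate and adverse events.
- Airway clearance ability: the only instrument is the SCSS, which "is a 6-point ordinal scale" running from 0 (no cough) to 5 (sustained vigorous coughing).
- Statistical methods {20a}: "Ordinal outcomes will be evaluated with Wilcoxon rank-sum tests". The sentence does not say what is ranked.
- Abstract, Methods: "Data will be analyzed using parametric or non-parametric tests for unadjusted between-group comparisons".

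No section conditions any comparison on a baseline value.

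**The concern.** The text allows two readings, and each has a cost.

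**The change is ranked.** The codes must be subtracted before they can be ranked, which gives them a spacing that an ordinal scale does not have. The usual reassurance that rank tests suit ordinal data covers ranks of a score, not ranks of a difference between scores. The room to improve is also 5 minus the baseline code, so the same benefit can show as a large or a small change depending on where the patient starts.

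**The Week 2 score is ranked.** The spacing problem disappears, but the baseline SCSS, which a change outcome requires to be measured anyway, plays no part in the comparison.

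The SCSS is the only measure behind the airway-clearance objective, and the trial was not sized for it. What is at stake is missing a real improvement in cough strength, or reporting an effect that is hard to interpret.

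**Working it through.** **1. What the stated sample size covers.** Inputs from Sample size calculation {14}: "we conservatively estimated a mean difference of 8% between groups", "we adopted a pooled SD of 9"%, and a "two-tailed *t*-test (*α* = 0.05, power = 0.90, allocation ratio 1:1"). The standardized difference is 8/9 = 0.889. Noncentral-t power is 0.893 at 27 per group and 0.904 at 28, so 28 per group is right. With 20% attrition, 28/0.80 = 35 per group. The plan's figures reproduce, but they concern MIP % predicted and say nothing about the SCSS.

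**2. Effect of subtracting codes.** Patient A moves from 0 to 2 and patient B from 3 to 5. Under the 0–5 codes both changes are 2, a tie. Relabel the top category 6 instead of 5, which preserves the order: A's change is still 2 and B's is now 6 − 3 = 3, so B ranks above A. The Week 2 ranks are the same under either labelling. The largest possible gain is 5 − baseline: 4 points from a baseline of 1, but 1 point from a baseline of 4.

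**3. Power.** The protocol gives no SCSS distribution, effect or correlation, so every input here is an assumption except 28 per arm (the planned number of completers) and two-sided 0.05.

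Model: latent baseline b ~ N(0,1); latent Week 2 value = ρb + √(1 − ρ²)·e + 0.7 × arm, with e ~ N(0,1). Both are cut into six categories holding 10/25/30/20/10/5% at baseline. Rank ANCOVA (Quade): rank both scores, regress Week 2 ranks on baseline ranks, and compare the residuals between arms.

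| Correlation ρ | Rank-sum on change | Rank-sum on Week 2 | Rank ANCOVA | Gain over change | Gain over Week 2 |
|---|---|---|---|---|---|
| 0.3 | 56% | 68% | 71% | 15 | 3 |
| 0.5 | 67% | 69% | 78% | 11 | 9 |
| 0.7 | 84% | 69% | 88% | 4 | 19 |
| 0.8 | 94% | 70% | 95% | 1 | 25 |

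Type I error was about 4–6% for all three tests. Allowing for simulation error and for scores clustered in the low categories, the gain over the change test is about 14–16, 10, 2–5 and 0–2 points at the four correlations. The gain over the Week 2 test runs from about 3 to about 26.

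**4. Sensitivity to the assumptions.** A second set used a shift of 0.6 SD, a common improvement of 0.5 SD in both arms, 35 per arm and 1,000 replicates. Power for change / Week 2 / rank ANCOVA:

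| ρ | Scores spread | Scores clustered low |
|---|---|---|
| 0.2 | 46 / 66 / 67% | 52 / 65 / 65% |
| 0.3 | 53 / 67 / 70% | 56 / 67 / 69% |
| 0.5 | 62 / 64 / 75% | 67 / 65 / 73% |
| 0.7 | 80 / 65 / 86% | 83 / 64 / 83% |
| 0.8 | 91 / 65 / 94% | 90 / 65 / 90% |

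With low-clustered scores at ρ = 0.7–0.8, rank ANCOVA gains nothing over the change test. At 28 per arm and ρ = 0.7 it was 73% against 74%, a difference within simulation error.

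**5. Proportional-odds model.** With arm and baseline SCSS, its likelihood-ratio test had type I error of 4.7–7.3% in the second set, and about 6–9% in a smaller run of 400 replicates. It is mildly liberal at this size.

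**The case against.** The strongest objection is textual. A reader might infer that the plan commits to ranking the difference of SCSS codes. It does not say so. The word for change heads a loose list that also contains the decannulation rate and adverse events, which cannot be changes from baseline. Where the protocol defines a change precisely, for MIP, it gives the time points. A rank-sum test on the Week 2 SCSS is a fair reading. This stands, so the equal-spacing criticism is conditional. What remains is that the two sections do not settle what is tested.

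A reader might also infer that the planned test is invalid or biased because of floor and ceiling limits. It is not: under randomization the baseline category adds noise, and the simulated error rates are nominal on both readings.

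Third, the power figures rest on assumed inputs, and a high correlation over two weeks cannot be excluded. That stands too. At 0.7 and above, ranking the change does much better than ignoring baseline and comes close to rank ANCOVA. A general claim that differencing costs a lot of power is therefore not supported.

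Finally, this is one secondary outcome in a trial that calls itself exploratory. That limits the weight of the point. It does not remove it, because the article itself fixes both the test and the absence of adjustment.

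**Conclusion.** The point holds in a limited form. The protocol leaves open whether the change or the Week 2 SCSS is ranked, and on either reading the unadjusted rank-sum test makes poor use of the baseline score. The consequence is reduced sensitivity and, if codes are subtracted, an effect without a clear meaning. Validity and the primary conclusion are untouched.

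The size depends on a correlation that the protocol does not give. At low correlation the loss is mainly against the change test (about 15 points at 0.3). At high correlation it is mainly against the Week 2 test (about 19 points at 0.7). Rank ANCOVA was the best of the three tests, or level with the best within simulation error, in every setting examined, so it is a safe choice when the correlation is unknown. These figures assume latent-normal scores, a shift of 0.6–0.7 SD and 28–35 patients per arm.

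**What to change.** In section {20a}, replace the sentence on ordinal outcomes, for the SCSS, with: *The Week 2 SCSS (not the difference of codes) will be compared between arms by rank ANCOVA (Quade), with baseline SCSS as covariate.* Align the list under Secondary outcomes by naming the SCSS at Week 2 rather than a change, and amend the abstract's reference to unadjusted comparisons accordingly.

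A common odds ratio from a proportional-odds model with arm and baseline SCSS may be reported as a descriptive effect estimate. State that it relies on proportional odds, that its interval may be slightly too narrow at this sample size, and that it may not agree exactly with the rank ANCOVA p-value. The unadjusted rank-sum test on the Week 2 score can stay as a supportive analysis.

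The cost is a few sentences and a protocol amendment before the blinded analysis. No extra patients or visits are needed, and no extra measurements, since a change outcome already requires a baseline SCSS. The rank ANCOVA needs only ranking, a linear regression and a comparison of residuals.

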### Interim analyses {21b}

No interim analyses are planned owing to the short trial duration (2 weeks) and the exploratory nature of the study.

### Methods for additional analyses (e.g., subgroup analyses) {20b}

No subgroup analyses are planned.

### Methods in analysis to handle protocol non‑adherence and any statistical methods to handle missing data {20c}

An ITT approach will be used for all primary and secondary outcome analyses. Multiple imputation will be employed to address missing data, ensuring statistical validity.

### Plans to provide access to the full protocol, participant-level data and statistical code {31c}

The results will be published in journals.

## Oversight and monitoring

### Composition of the coordinating center and trial steering committee {5d}

The trial steering committee (TSC), which is composed of experienced professionals, is responsible for ensuring scientific rigor, ethical compliance, and operational integrity throughout the clinical trial. Its structure and functions are as follows:

Composition:A senior physician chairperson.Multidisciplinary medical experts (e.g., biostatistics, clinical practice).An independent ethics specialist.Roles and responsibilities:Evaluate trial design, protocols, and informed consent documents for scientific validity and regulatory adherence.Monitor trial progress, safety outcomes, and ethical standards.Provide expert recommendations to resolve challenges and enhance trial quality.Safeguard participant rights and welfare through ongoing oversight.This streamlined framework maintains accountability while emphasizing collaborative oversight across scientific, ethical, and operational domains.

### Data monitoring committee (DMC) {21a}

No independent DMC is established, as this is a low-risk, short-term trial. Safety monitoring is performed by the coordinating center.

### Adverse event reporting and harms {22}

Although this study is associated with minimal known risks, participants are instructed to immediately notify the responsible physiotherapist of any adverse or serious events. The possible side effects may include fatigue, dizziness, or transient decreases in blood oxygen saturation. Any adverse events will be promptly reported to the Institutional Research Ethics Committee by the designated principal investigator.

### Frequency and plans for auditing trial conduct {23}

The Trial Steering Committee will conduct biweekly audits throughout the study period. During these meetings, the committee will review participant recruitment progress, the informed consent process, adherence to the study protocol, and all recorded adverse events.

